### End points

The primary end point will be overall survival (all-cause mortality); secondary end points will include disease progression, treatment-limiting adverse events, and treatment failure (Table 1). Data from these protocol-defined end points will be used to analyze treatment patterns and therapeutic outcomes as described in the following sections.

**Table 1 T1:** Definitions of study end points

**Primary end point**
Overall survival
Number of days from date of treatment initiation to date of death. Death will be verified by sites based on death certificates or via caregiver, relative, or health care provider, and death information source will be captured in data collection. Surviving patients will be censored from last date of treatment assessment.

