## Methods

### Study design

The global HCC BRIDGE study is a multiregional longitudinal cohort trial including patients diagnosed with HCC from January 1, 2005, to June 30, 2011 [10]. Patients enrolled in the study will be followed from the date of HCC diagnosis to December 31, 2011, or date of death, whichever comes first. The HCC BRIDGE China national study comprises the portion of the global HCC BRIDGE study conducted within mainland China. To ensure that the national study is geographically representative, it was designed to include patients enrolled at sites from all 7 traditional regions across China (North, North-East, East, South, South-West, North-West, and Central).

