### Study sites

Sites have been selected for inclusion in the China national study on the basis that (1) they are tertiary care centers providing surgical and routine follow-up care for patients with HCC or are oncology centers that care for these patients; (2) the type and proportion of etiologies for HCC are consistent with the Chinese national average; and (3) the HCC screening practices, when used, are in accordance with Chinese national standards. In addition, sites may be selected if the patient population was, on a prior occasion, used to characterize the Chinese national HCC population for other research purposes, for example during evaluation of national HCC incidence/prevalence rates or the establishment of national HCC staging systems.

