### Patients

All patients enrolled in the HCC BRIDGE study must meet 3 key inclusion criteria: (1) diagnosed with HCC between January 1, 2005, and June 30, 2011, in accordance with American Association for the Study of Liver Diseases/European Association for the Study of the Liver guidelines [11]; (2) aged at least 18 years at the time of HCC diagnosis; and (3) received or receiving treatment for HCC through a site enrolled in the HCC BRIDGE trial. Patients participating in other clinical trials will be included in the study if the patient is enrolled in a single-arm clinical trial, enrolled in a randomized clinical trial of HCC adjuvant therapy, or was not selected to receive active treatment in a randomized clinical trial that was conducted between 2005 and 2007. Any patient whose first active HCC-directed treatment is received via participation in a randomized clinical trial of primary HCC therapy will be excluded from the current study, since this treatment regimen would have been determined by a study protocol rather than by the treating physician. Similarly, patients included in the China national study who subsequently enroll in such a trial will be censored from the study at that time point. Patients with unknown month and year of HCC diagnosis or of the first visit at the site of inclusion will be excluded. Furthermore, to preserve regional representation within China, patients who reside outside the province of interest for a particular study site will also be excluded. Finally, in order to avoid selection bias when the number of eligible patients at a site exceeds the number allowed according to study sample size calculations, an enrollment scheme will be adopted such that the same number of consecutive patients are enrolled each month. For example, in the first year of data entry, if a site is to enroll 200 patients, approximately 17 consecutive patients diagnosed with HCC will be enrolled in each month. If there are less than the specified numbers of patients in any given month, we ask that the corresponding number of extra patients be enrolled in the following month.

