### Data collection

The following data will be systematically collected for all enrolled patients: (1) date of diagnosis and/or date of first HCC visit; (2) demographic and clinical characteristics at the time of diagnosis/first HCC visit and at all occurrences of new treatment intervention during the study period via medical chart review; (3) data on variants of HCC diagnosis, for example, mixed HCC, fibrolamellar HCC, and on the additional diagnosis of cholangiocarcinoma; (4) data on the use of currently available HCC treatment approaches during the study period from medical chart review; (5) data on the use of new treatments for HCC if they become available and are used prior to study end; (6) data on hospitalizations, clinical visits, and visits to other health care professionals, with collection of hepatic function, tumor assessments, and laboratory values according to clinical judgment; and (7) data on method of payment for health care utilization. All data will be collected retrospectively and prospectively at study sites in order to account for patient records over the full duration of the study; data collection is expected to be complete by June 2012. All sites will enter data into an electronic data capture system developed by Outcome Sciences, Inc. (Cambridge, MA, USA). Outcome Sciences will manage the data system, including monthly data monitoring and cleaning, site queries, and check of invalid clinical values determined a priori by study investigators. All data collection procedures will comply with Chinese privacy and confidentiality requirements.

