### Data analysis

To evaluate therapeutic approaches to HCC in China, the number and percentage of patients using each treatment (plus any new treatments that are approved and used within the study period) will be determined for each study year, in total and stratified by disease stage and site. Treatment patterns will also be assessed by disease stage for each study year. Patient characteristics will be stratified by disease stage and by site for each study year.

To assess therapeutic outcomes, age- and gender-adjusted rates will be calculated for each study end point. Cox proportional hazard models will be used for the time-to-event end points (overall survival and disease progression) to determine hazard ratios for each treatment approach, and Kaplan-Meier curves will be generated. Logistic regression models will be used for categorical end points (treatment-limiting adverse events and treatment failure). Covariates for the models will include disease stage, gender, age, duration of disease, etiology of disease, liver status, tumor size/spread, surgical intervention/number of interventions, and number of comorbidities; analyses will be conducted at the site and country level. The same analysis plan will be adopted for the evaluation of survival and other clinical end points with sorafenib versus other therapies, except that "treatment" will be included as a covariate. Further analyses will be conducted to evaluate clinical characteristics and demographics of patients treated with sorafenib versus other treatments for HCC. In addition, data collected will be used to analyze additional aspects related to HCC epidemiology and management in China (Table 2). All tests of statistical significance will be carried out at the 0.05 level.

**Table 2 T2:** Additional aspects of HCC management for potential evaluation using data from the HCC BRIDGE China national study.

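### Overall survival runs from an unspecified start of treatment, so for patients first treated elsewhere, time survived before reaching the site can be counted as time at risk

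*Protocol article*

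**What the plan says.** The time origin of the primary end point is in Table 1: "Number of days from date of treatment initiation to date of death". It is not tied to the first treatment anywhere, the first at the site, or the start of the intervention being analysed.

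Under Patients, the third inclusion criterion is "received or receiving treatment for HCC through a site enrolled in the HCC BRIDGE trial". Earlier treatment elsewhere does not exclude a patient, unless the first active treatment came from a randomized trial of primary therapy. The same section separates diagnosis from arrival at the site: "Patients with unknown month and year of HCC diagnosis or of the first visit at the site of inclusion will be excluded".

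Under Study design, observation starts at diagnosis: "Patients enrolled in the study will be followed from the date of HCC diagnosis to December 31, 2011, or date of death, whichever comes first". Under Data collection, "All data will be collected retrospectively and prospectively at study sites in order to account for patient records over the full duration of the study". Under Study sites, one selection criterion is that "they are tertiary care centers providing surgical and routine follow-up care for patients with HCC or are oncology centers that care for these patients".

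The Data analysis section plans Kaplan-Meier curves, Cox hazard ratios for each treatment approach, and analyses at site and country level. It gives the first-visit date no role.

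**The concern.** Take two hypothetical patients diagnosed and first treated at a hospital outside the study in 2006. One dies in 2007 without reaching a participating site and can never be enrolled. The other arrives in 2009, is treated there and is eligible. If that patient's clock starts in 2006, about three years are credited during which an enrolled patient could not have died. This is left truncation, also called immortal time before entry.

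Counting such time at risk enlarges the early denominators without the matching deaths, so estimated survival is too high. Two uses of the data are exposed:

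- absolute survival for China and for each site;
- comparisons between treatments or sites whose patients differ in how often they were first treated elsewhere.

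Sampling consecutive patients by month of diagnosis does not help, because the site never sees those who died first. Among the Cox covariates, duration of disease may shift the modelled hazard. It does not take the pre-entry time out of the risk set, and it does nothing for an unadjusted Kaplan-Meier curve.

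**Working it through.** The article states no survival figure, event count or referral share, so there is no plan figure to reproduce. The check asks which way the bias goes and how large it could be.

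**Inputs.** From the article: the clock starts at treatment initiation, and enrolment is possible only for patients alive to be treated through a site. Assumed, not in the documents:

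- exponential survival with true median m of 6, 12 or 24 months;
- a share p of 10, 30 or 50% of source patients first treated elsewhere;
- an exponential lag to site entry with mean g of 1, 3 or 6 months, unrelated to prognosis.

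**Formula.** Let λ = ln 2 / m, μ = 1/g and q = λ/(λ + μ). A referred patient dies before arrival with probability q, so a fraction pq of all source patients is never seen. If everyone enrolled is counted at risk from day 0, the curve is

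S(t) = e^(−λt) × [1 − pq·e^(−μt)] / (1 − pq),

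and the true curve is e^(−λt). The factor on the right exceeds 1 for every t > 0 when pq > 0, so the direction is upward. It equals 1 when p = 0.

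**Worked case** (m = 12, p = 50%, g = 6):

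- λ = 0.0578, μ = 0.1667, q = 0.0578/0.2244 = 0.2574, pq = 0.1287.
- At 12 months, e^(−λt) = 0.500 and e^(−μt) = e^(−2) = 0.1353.
- S(12) = 0.500 × (1 − 0.0174)/0.8713 = 0.564, against a true 0.500.

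**Simulation.** With 400,000 source patients per scenario and administrative censoring at 6 to 84 months, the results were:

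| True median (months) | Referred | Kaplan-Meier median from treatment start, mean lag 1 to 6 months | With delayed entry at site arrival |
|---|---|---|---|
| 6 | 10% | 6.10 to 6.22 | 5.98 to 6.00 |
| 6 | 50% | 6.48 to 7.46 | 5.99 to 6.02 |
| 12 | 10% | 12.10 to 12.40 | 11.99 to 12.01 |
| 12 | 30% | 12.27 to 13.23 | 11.98 to 12.00 |
| 12 | 50% | 12.47 to 14.20 | 11.99 to 12.01 |
| 24 | 10% | 24.08 to 24.53 | 23.96 to 24.02 |
| 24 | 50% | 24.42 to 26.78 | 23.89 to 24.11 |

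**Range.** The smallest overstatement is 24.08/24 − 1 = 0.3% (the formula gives 24.10, or 0.4%; the gap is simulation error). The largest is 7.46/6 − 1 = 24%. For a 12-month true median, 12-month survival reads 0.503 to 0.564 instead of 0.500.

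**Null case.** With nobody referred, the medians are within simulation error of the truth. Starting the clock at site arrival also returns the true median, here because the assumed hazard is constant.

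**Comparisons.** Two treatments with the same true 12-month median and a mean lag of 6 months would show 12.40 months at 10% referred and 14.20 at 50%. That is an apparent gap of 1.8 months with no real difference. Equal referral mixes would leave little such gap.

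**The case against.** The strongest reply is that the start of treatment may mean treatment at the site, or the start of each intervention analysed. The inclusion criterion is framed around treatment through a site, the secondary end points in Table 1 are counted by treatment intervention, and the Cox models give hazard ratios by treatment approach. If the clock starts at treatment given at the site, this bias is zero. That stands, and it is why the point is conditional. But the primary time origin should not depend on a choice of reading, and observation from diagnosis makes the pre-arrival reading a natural one.

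The scenario may also be uncommon. The abstract speaks of newly diagnosed patients, those living outside the site's province are excluded, and the sites also give routine follow-up care. These limits narrow the problem, but referral within a province remains possible.

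A reader might infer that the reported survival will be too favourable overall. The documents do not support that. Table 1 censors survivors at their last treatment assessment, while deaths may be traced through certificates or relatives, and this pushes estimates down. Only one component of bias is shown here, and the net direction is not settled. The opposing component is no remedy either, since nothing makes the two cancel within a treatment or site.

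Handling of the risk set is often left to an analysis plan, which is not shown. The absence of a delayed-entry sentence is therefore not the point. The point is the origin that Table 1 does fix, set against the entry rule.

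**Conclusion.** The concern holds in conditional form. Table 1 and the eligibility rule together allow survival before site entry to be counted as time at risk, and nothing in the article prevents it. For any patient so affected the component bias is upward, and it can distort comparisons between treatments or sites with different referral shares.

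Its size cannot be known from the article. The range of about 0.3% to 24% in the median rests on assumed exponential survival, referral shares, lags, and lag times unrelated to prognosis. The top figure needs a 6-month median, half of patients referred and a 6-month mean lag. With a 12-month median and 10% referred it is about 1 to 3% (12.10/12 to 12.40/12).

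A reader might also want the same correction for time to progression. That does not follow directly. Patients who progressed before arrival would contribute no time at risk under delayed entry and would drop out, so that end point needs separate thought.

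**What to change.** 1. State in Table 1 which treatment starts the overall-survival clock.
2. If it can precede site entry, keep that origin but enter each patient into the risk set only at the later of treatment initiation and first treatment through the site, in all Kaplan-Meier and Cox analyses of overall survival. First treatment through the site is the better entry point because it is what makes a patient eligible. Entry at the first visit would leave the gap from visit to site treatment death-free by selection. The first visit is the minimum fallback, since its month and year are already required.
3. Add a sensitivity analysis in patients whose first treatment for the cancer was given at the site. This also guards against referral timing that depends on prognosis, which delayed entry alone does not handle.

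The cost is a sentence or two in Table 1 and Data analysis, and a check that the data capture identifies which treatments were given at the site. Precision in early follow-up falls slightly, and entry dates may be accurate only to the month. If few patients were treated elsewhere first, the results will hardly change.

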### Loss to follow-up

Throughout the HCC BRIDGE China national study, patients are expected to leave via loss to follow-up, by consenting to enter a randomized clinical trial of primary HCC treatment, or at death. Death certificate searches or interviews with the patient's caregiver, relative, or health care provider will be used to verify deaths. The inability to verify deaths is expected for 5% of patients in the study. Sample size calculations have been adjusted accordingly to account for this level of missing data for the primary end point of the study.

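### Overall survival stops survivors' time at the last treatment assessment but counts deaths to the data cut, so censoring is informative; the size and net direction of the bias depend on an unstated gap

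*Protocol article*

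**What the plan says.** Table 1 of the protocol article measures overall survival as "Number of days from date of treatment initiation to date of death". For those who have not died it adds: "Surviving patients will be censored from last date of treatment assessment".

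Deaths come from sources that do not depend on treatment visits: "Death will be verified by sites based on death certificates or via caregiver, relative, or health care provider". The Loss to follow-up section repeats these sources as the means of verifying deaths and warns: "The inability to verify deaths is expected for 5% of patients in the study".

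The Study design section has patients "followed from the date of HCC diagnosis to December 31, 2011, or date of death, whichever comes first".

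The Data analysis section applies Cox models and Kaplan-Meier curves to overall survival. The Comparator groups section matches sorafenib patients of 2008 to 2011 to historic controls from 2005 to 2007. The Discussion notes that clinicians and patients, not a schedule, determine when assessments take place.

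**The concern.** Events and survivors are observed over different windows. Take two patients with the same last treatment assessment, well before the cut. One dies afterwards, and the death enters at its true, later date. The other lives to the cut and contributes none of that interval. Whether a patient stays in the risk set after the last assessment thus depends on whether the patient will die before the cut. Kaplan-Meier and Cox methods assume that this is not so.

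At stake are the survival curves and adjusted death rates, and also the comparison of sorafenib-era patients with historic controls. The rule acts only on survivors, and the later era has many more of them at the cut.

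Table 1 uses the same censoring date for time to progression, treatment-limiting adverse events and treatment failure. It may suit those end points. It does not suit all-cause death followed to a calendar date.

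**Working it through.** The article gives no median survival, event count or assessment interval, so there is no figure of its own to reproduce.

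**Inputs from the article**
- Accrual of "patients diagnosed with HCC from January 1, 2005, to June 30, 2011" and the cut of December 31, 2011. Potential follow-up is therefore about 6 to 48 months for diagnoses from 2008 to mid-2011, and 48 to 84 months for 2005 to 2007.
- Unverifiable deaths: 5%, taken here as 5% of deaths.

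**Assumptions**
- Exponential survival with a true median of 8, 12 or 24 months.
- Uniform entry, with treatment starting at diagnosis.
- Gap G between last assessment and cut exponential with mean g.

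**Formula.** Let T be time to death, C potential follow-up and λ = ln 2 / median.
- Correct risk set at t: R(t) = e^(−λt) · P(C ≥ t).
- Wrongly removed by the rule, namely survivors whose last assessment came before t: D(t) = P(T > C, C ≥ t, C − G < t) = E[e^(−λC) · e^(−(C−t)/g); C ≥ t].
- Estimated hazard: λ · R(t) / (R(t) − D(t)). This exceeds λ whenever D(t) > 0.

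**Numbers put in** (median 12, g = 6, t = 12, C uniform on 6 to 48)
- λ = 0.0578 and R = 0.5 × 36/42 = 0.429.
- With k = λ + 1/6 = 0.2244, D = [e^(2 − 12k) − e^(2 − 48k)] / (42k) = (0.500 − 0.0002) / 9.426 = 0.053.
- Hazard inflation at month 12: 0.429 / (0.429 − 0.053) = 1.14.

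**Kaplan-Meier median, 2008 to mid-2011 patients, all deaths verified** (simulation; the formula integrated numerically agrees to 0.1 month)

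| True median | g = 1 | g = 3 | g = 6 | g = 12 |
|---|---|---|---|---|
| 8 | 7.9 | 7.8 | 7.5 | 7.2 |
| 12 | 11.8 | 11.5 | 11.0 | 10.3 |
| 24 | 23.5 | 22.3 | 20.9 | 18.8 |

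Gaps of 1 to 3 months cost about 1% to 7% of the median. With survivors censored at the cut, the medians return to 8.0, 12.0 and 24.0.

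**If assessments end early.** If assessments are monthly and stop for good after a mean of 6 months, with 5% of deaths unverified, a true median of 12 is reported as about 9.7.

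**Adding the 5% unverified deaths** (censored at their own last assessment). True medians of 8, 12 and 24 become 8.3, 12.4 and 24.6 at a 1-month gap, and 8.1, 11.9 and 23.3 at a 3-month gap.

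**2005 to 2007 patients.** The median is essentially unchanged and the crude death rate rises by at most about 7%, because few survivors remain. With a true median of 12 months, about 3% are alive at the cut, against about 27% in the later era.

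**Later versus earlier era, equal true hazards and equal gaps.** The hazard ratio is 1.05 to 1.10 (g = 3), 1.10 to 1.16 (g = 6) and 1.19 to 1.35 (g = 12) over the three medians. Control runs censored at the cut gave 0.97 to 1.03, which shows the simulation noise. A repeat with 150,000 patients per era gave 1.05 to 1.10, 1.11 to 1.20 and 1.16 to 1.37. Leaving 5% of deaths unverified in both eras did not change these ratios materially.

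**The case against.** The strongest reply is that treatment assessment is undefined and may mean any clinical or tumor assessment. The Data collection section gathers visits, hospitalizations, tumor assessments and laboratory values over the whole study. If survivors are seen every month or two up to the cut, the gap is short and the effect small. This stands as a limit on size. It does not make the rule valid, and nothing in the article requires an assessment near the cut.

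A reader might infer that reported survival is bound to be too short. The article does not support that. Unverifiable deaths act in the opposite direction, and at a mean gap of 1 month the net bias in the examples is toward longer survival.

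A reader might also infer that hazard ratios between treatments are biased because a continuous drug and a one-off procedure are assessed on different schedules. With equal true hazards, mean gaps of 1 versus 6 months would give a spurious ratio of 1.06 to 1.13. But the article states no such difference. It says only that timing is not standardised. The era effect needs no such assumption.

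Finally, the article condenses a fuller protocol that might define the date further. The rule is nevertheless stated explicitly here, and a fuller document that censored otherwise would contradict it. The limitation on data collection bias in the Discussion is general and neither names nor corrects this asymmetry.

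**Conclusion.** The point holds in conditional form. The stated rule makes censoring for the primary end point depend on survival, and taken alone it overstates mortality. For 2008 to mid-2011 patients the median falls by about 1% to 7% at mean gaps of 1 to 3 months. At 12 months it falls by about 10% (7.2 for 8) to 22% (18.8 for 24). The net direction at short gaps is open because of the unverifiable deaths.

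The comparison of eras can be biased against the later, sorafenib-era group even when gaps are equal. That result is for unmatched groups with identical exponential survival; matching on age, sex, Child-Pugh status and stage does not address the difference in follow-up. Bias between treatments beyond this arises only if their assessment gaps differ. All sizes rest on assumed medians and gaps.

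**What to change.** For overall survival, replace the censoring sentence in Table 1 as follows:

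- Censor at December 31, 2011 when the patient is confirmed alive on or after that date.
- Otherwise censor at the last date known alive from any collected source: visit, hospitalization, laboratory value or contact.
- For patients whose status at the cut is unknown, count deaths only over the window in which survival would also have been recorded. Without this, the last-known-alive date keeps the same asymmetry.
- Report the last-treatment-assessment rule as a sensitivity analysis, and keep it for the treatment-related end points.

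Cost: a revised definition, one last-known-alive date in the data capture system, and some site effort to record vital status at the cut. That effort is new work, because the planned searches and interviews are described only as verifying deaths, not as confirming that patients are alive. The other dates needed come from data already collected.
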